## Methods

### Recruitment

Participants for the alpha and beta phases will be patients with an asthma diagnosis, as described above. Participants should be 18 years or older, able to communicate fluently in English, and willing to use WhatsApp on their mobile phones.

Participants will be compensated for their time (which involves trying the chatbot at least once and filling out a pre- and postquestionnaire on day 1 and 28, respectively) with a £10 (approximately US $12) voucher. The research study questionnaires will be provided in Qualtrics, separate from the chatbot so as not to interfere with the experience of the chatbot itself.

A total of 300 individuals will be recruited in three waves. Only approved phone numbers (of people who have consented to the study) will be able to interact with the chatbot.

Recruitment will be done over four channels:

YouGov: 120 adults with diagnosed asthma will be recruited through YouGov. We expect roughly 10% of the cohort who participated in the survey or 20% of those who expressed interest in the chatbot.Facebook: 60 participants with self-reported asthma will be recruited through Facebook’s advertising engine.Healthily: 60 participants with self-reported asthma will be recruited through Healthily (a medically approved self-care platform). Healthily will advertise the study in the “Asthma Hub” accessed by people with, or interested in, asthma. The timeline will be as the one above. People using Healthily are interested in self-care and pay £29.99 (approximately US $36.70) per year to access it.Asthma + Lung UK social media: 60 participants with self-reported asthma will be recruited through social media channels managed by our partner organization.

The social media channels will direct people to a web page that will screen for inclusion criteria. Those who meet the criteria will be invited to participate, asked for informed consent, and directed to the prequestionnaire and then to the chatbot in WhatsApp on their mobile phones.

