Recruitment and chatbot use will be phased to allow for iterative improvements. We will start recruitment through YouGov. The first batch of 20 individuals will use it for 1 week, and their feedback and engagement measures will be used to inform a new iteration of improvements. The same will be done with a second batch of 20 people. We refer to these groups as alpha testing in Figure 1. The third and final batch of 260 people will be drawn from the remaining recruitment channels and will use the system for 28 days. We refer to this group as beta testing in Figure 1.

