### Procedure

We estimate that the average conversation will take less than 15 minutes. Participants will be sent randomly timed messages once a week to invite them to track their asthma risk during the period of the study. After the data collection period (28 days), participants will respond to survey items related to the quality of the interaction. At day 28, they will be sent a final reminder inviting them to complete the exit questionnaire with a link to a Qualtrics form. A follow-up WhatsApp message sent 3 months later will ask users to report if they had an asthma exacerbation within the last 3 months (since they used the bot), and they will have one additional month (which means 4 months from using the bot) to provide this information on exacerbations.

For clarity, if the project were to start on January 1, the first group would finish on January 7. Feedback would take a week to address, and the second group would start on January 14, finishing on January 21. The third batch would start on February 1 and finish on March 1; a follow-up message asking about any asthma exacerbations would be sent on June 1 (allowing them to respond until July 1).

The outcome variables and associated measures are presented in Table 1.

**Table 1 table1:** Outcome variables and associated measures.

Variable	Measure
Acceptability, usability, and satisfaction of the chatbot, including the risk assessment dialogue and follow-up dialogues on asthma triggers and management strategies for improvement of asthma control	We will combine the following standard technology satisfaction measures: Task completion (% complete risk assessment process vs drop-out rate) Net Promoter Score question: “how likely are you to recommend the chatbot to someone else with asthma on a scale from 0 to 10” User satisfaction questions for each dialogue topic (eg, “Did you measure your risk using the chatbot? How useful did you find this feature?”) Open-ended questions on what worked well and what did not, and how the chatbot could be improved
Motivational quality, engagement, and user experience in relation to basic psychological needs	Motivation, Engagement, and Thriving in User Experience questionnaire [14]
Alignment between expected and calculated risk, and whether the calculated result changes risk self-assessment	Self-report questions on risk score expectation vs result and trust in result

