### Analysis Plan

We seek to answer the following questions:

Are there differences among the dialogue topics with regards to engagement? If so, which topic is most engaging? Do participants engage more, less, or equally with the artificial intelligence–enhanced motivational interviewing informed dialogues versus the health education branching dialogues? Does engagement with any topic correlate with better health or technology satisfaction outcomes?Although the goal of the study is not assessing the efficacy of the intervention, will the group’s asthma control improve at the end of the 4 weeks? A future randomized controlled trial will explore the efficacy with appropriate power and rigor, but this study might give initial indications of effect sizes.Did the iterative development approach improve outcomes? To test if the alpha and beta predict different effects, and assuming they have nonnormal distributions, we will use the nonparametric Kruskal-Wallis test.

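### The alpha-versus-beta test cannot attribute a difference to iterative development, because exposure length coincides fully with chatbot version and recruitment channel largely does

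*Protocol article*

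**What the plan says.** The Analysis Plan poses the question "Did the iterative development approach improve outcomes" and gives one method for it: "To test if the alpha and beta predict different effects, and assuming they have nonnormal distributions, we will use the nonparametric Kruskal-Wallis test". It states no covariate, stratification, restriction or common time window.

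The Recruitment section defines the groups:

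- **Alpha:** "We will start recruitment through YouGov", then "The first batch of 20 individuals will use it for 1 week". For the next batch, "The same will be done with a second batch of 20 people". That makes 40 people with 1 week of use each.
- **Beta:** the final 260 come from the channels that remain and "will use the system for 28 days".

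The channel quotas in the same section are 120 for YouGov and 60 each for Facebook, Healthily and Asthma + Lung UK social media. Participants in general complete a "pre- and postquestionnaire on day 1 and 28, respectively", with no exception for the 1-week batches.

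The Procedure section gives one prompt per week and a worked calendar. Batch 1 runs from 1 to 7 January, and for batch 2, "Feedback would take a week to address, and the second group would start on January 14, finishing on January 21". Beta runs from 1 February to 1 March.

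**The concern.** The question is about chatbot version, but the two groups differ in more than version. No alpha user has 28 days of use and no beta user has only 7, so exposure length and version cannot be separated. Alpha users receive about one weekly prompt and beta users about four. Recruitment starts with YouGov, whereas most or all of beta comes from elsewhere. The article itself describes one of those other channels, Healthily, as serving paying users with an interest in self-care. Calendar period differs as well.

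Engagement is a central outcome of the study, and both time available and type of user can plausibly affect it. The planned comparison could credit iteration with an improvement that comes from longer exposure or a keener channel. It could equally hide a real improvement if those factors pull the other way. The limitations in the Discussion do not mention this.

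**Working it through.** **1. The plan's own totals.** Channels: 120 + 60 + 60 + 60 = 300. Batches: 20 + 20 + 260 = 300. Both agree with the stated sample. The article gives no power calculation to reproduce.

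**2. Channel mix.** The three other channels supply 3 × 60 = 180, which is fewer than 260. If the quotas hold and the first 40 are all YouGov, then 120 − 40 = 80 YouGov participants must be in beta. Beta is then 180/260 = 69% non-YouGov and 80/260 = 31% YouGov. Read literally, drawing beta from the remaining channels would make it wholly non-YouGov, but those channels cannot fill 260 places. The two statements do not fit together as written.

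**3. Exposure.** Alpha has 7 days and beta 28, a ratio of 4, with no overlap. Weekly prompts: about 1 against about 4.

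**4. Exposure illustration, no version effect.** Assumptions, none of them from the article: two groups of 40 and 260; two-sided 5% level; one session for everyone plus overdispersed (gamma-Poisson, shape 0.5 or 1) extra sessions at a first-week rate r of 0.3, 0.5 or 1.0. Mean extra sessions:

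- alpha, 7 days: r
- beta, 28 days, steady use: 4r
- beta, 28 days, use halving weekly: r(1 + 0.5 + 0.25 + 0.125) = 1.875r

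| Comparison of session counts | Kruskal-Wallis rejects |
|---|---|
| 7-day v 28-day totals, steady use | about 95-100% |
| 7-day v 28-day totals, use halving weekly | about 27-68% |
| First 7 days in both groups | about 5% |

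The test holds its nominal level once the window is common. The excess comes from the comparison, not from the test.

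**5. Channel illustration, no version effect.** Assume that non-YouGov users differ from YouGov users by 0.3 to 0.5 SD on a normally distributed outcome. With 80 YouGov users in beta the mean shift is diluted to 0.3 × 180/260 = 0.21 SD and 0.5 × 180/260 = 0.35 SD, and the test rejects in about 21% and 51% of runs. With no YouGov users in beta it rejects in about 41% and 82%.

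**6. Assessment time.** A day-28 form for batch 1, which starts on 1 January, falls on about 28 January. That is after batch 2 ends (21 January) and before beta starts (1 February). If alpha forms are taken at day 28, assessment time matches beta but exposure does not. If they are taken at day 7, neither matches. The article does not say which applies.

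**7. Cost of a like-for-like comparison.** Detectable difference at 80% power, two-sided 5%, in SD units: (1.96 + 0.84) × √(1/n₁ + 1/n₂).

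- 40 v 260: 2.80 × √(0.0250 + 0.0038) = 0.48
- 40 v 80: 2.80 × √(0.0250 + 0.0125) = 0.54 (0.55 with the t distribution)
- 20 v 20, the two alpha batches: 2.80 × √(0.05 + 0.05) = 0.89

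**The case against.** The strongest reply is that this is a single-arm feasibility study. The Analysis Plan disclaims any aim of assessing efficacy and defers that to a randomised trial. The iteration question comes last, and no progression or safety decision hangs on it. That stands, and it lowers the severity. It does not cure the mismatch: the article names a hypothesis test for this question, and the test cannot answer it. Common windows and covariates are often left to an analysis plan, but no adjustment can separate exposure length from version when the two coincide; the comparison itself has to be redefined.

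A second reply is that the high rejection rates depend on cumulative counts. That also stands. The Analysis Plan says only outcomes, and most Table 1 measures are ratings or questionnaire scores. For those the size of any exposure bias is unknown.

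Three stronger readings are tempting and are not supported:

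- **That Kruskal-Wallis is the wrong test, being omnibus and non-directional.** The article contrasts alpha with beta and labels both 20-person batches alpha. With two groups the test is equivalent to the Wilcoxon rank-sum test, and the direction can be read from the data. A trend test would be a preference.
- **That a day-28 alpha questionnaire could not inform iteration.** Batch 1's form would come too late for batch 2 but could still inform the beta version. The article also bases iteration on batch feedback and engagement measures and does not say that these are the postquestionnaire.
- **That channel is completely confounded with version.** If the quotas are met, about 80 beta users come from YouGov.

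**Conclusion.** The concern holds as a problem of attribution. Exposure length is fully confounded with chatbot version, channel is largely so, and calendar time differs too. Whatever the alpha-versus-beta test shows, it cannot be read as the effect of iteration.

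The simulated rates in the working show that the distortion can be large for outcomes that accumulate with use, and that a plausible channel difference alone could produce a false signal. They rest on assumed session rates, decay and channel shifts, and they are not estimates for this study. A reader might infer that a false positive is nearly certain whatever outcome is tested; the article does not support that for ratings or for asthma control.

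This should be fixed, but it is not critical: the question is exploratory and secondary to feasibility and engagement.

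**What to change.** 1. Reconcile the channel quotas with the description of the final batch, and state how many YouGov participants are in beta.
2. Make the main version comparison on log-based outcomes truncated at day 7 for every participant, within YouGov (40 alpha v 80 beta if the quotas hold). Add an all-channel analysis adjusted for channel as sensitivity. Report differences with 95% confidence intervals. The Kruskal-Wallis or rank-sum test may stay.
3. Reconcile the day-28 postquestionnaire with the 1-week alpha batches. Leave questionnaire outcomes and change in asthma control out of this comparison unless both exposure and assessment time match.
4. Call the result exploratory, because calendar time still differs. If beta turns out to have no YouGov users, label the alpha-beta comparison descriptive only.

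The cost is mainly wording: it needs only timestamped use logs and each participant's recruitment channel. The statistical price is a detectable difference of about 0.55 SD (40 v 80) instead of about 0.48 SD (40 v 260). The two alpha batches share channel and duration and could be compared descriptively, but 20 v 20 would detect only about 0.89 SD.

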Changes to asthma understanding, attitudes, and behaviors following use of the app	Self-report questions on changes to understanding, attitudes, and behaviors related with asthma self-management
Self-reported level of asthma control and symptoms, including changes over time	The Asthma Control Questionnaire [20] will be asked at the beginning and end of the study
Patterns of engagement and satisfaction for different types of users, particularly those who do not access professional services and those with poor asthma control	Analysis of pre- and postquestionnaires and additional self-report questions on use of professional services (eg, “when was the last time you spoke to a GP about asthma”)

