## Discussion

People living with asthma need support to improve the accuracy of their risk self-assessment and asthma self-management, increase their access to professional care, and ultimately reduce asthma attacks and emergencies. Digital health technologies like apps offer new ways to address these but are often not used. In our survey, only 7% of people with asthma had used an asthma app. On the other hand, most use messaging platforms; in particular, 85% use WhatsApp. This has led us to develop a chatbot intervention to be delivered through WhatsApp that estimates the risk of an asthma exacerbation and provides recommendations on how to manage it better.

Our proposed study will evaluate the feasibility of this WhatsApp chatbot, with a particular focus on improving our understanding of the drivers and obstacles of engagement. While the chatbot has been designed and developed using the best practices available, such understanding will allow for better health chatbots in the future.

With respect to study limitations, since this is only a feasibility study, we are recruiting a relatively low number of participants (N=300). As such, we do not expect to find sex or age differences within the current sampling, and we do not expect to measure statistically significant improvements in asthma control over the 28 days. Furthermore, as we rely on self-report of diagnosed asthma (including having been prescribed a blue reliever inhaler that is only available through prescription), we could get some responses from someone who incorrectly answered the screening questionnaire.

In the future, findings from this study will be validated as part of a randomized controlled trial to determine whether the chatbot can measurably improve health outcomes. All these results will inform the development process of future chatbots in the health domain.

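### The iteration question rests on an unadjusted Kruskal-Wallis test of 40 versus 260 with no stated effect measure; adjust ACQ for its baseline and report an estimate with an interval

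*Protocol article*

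**What the plan says.** The last question in the Analysis Plan of the protocol article is "Did the iterative development approach improve outcomes". The method follows directly. To see whether the alpha and beta phases lead to different effects, and on the assumption that the distributions are not normal, the article says "we will use the nonparametric Kruskal-Wallis test". This is the only statistical test that the section names.

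The Recruitment section defines the groups. Alpha is two small batches: "The first batch of 20 individuals will use it for 1 week", and "The same will be done with a second batch of 20 people". Beta is the rest: "The third and final batch of 260 people will be drawn from the remaining recruitment channels and will use the system for 28 days". Recruitment begins with YouGov, so the alpha batches come from there.

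Table 1, under Procedure, lists the outcomes. For the ACQ it says that the questionnaire "will be asked at the beginning and end of the study". The recommendation score, dialogue satisfaction, task completion and user-experience measures concern the chatbot itself, so they have no value before use.

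**The concern.** The question is about improvement, which has a direction and a size. The named test addresses only whether the two phases differ. With two groups, Kruskal-Wallis is equivalent to the two-sided Wilcoxon rank-sum test. It carries no covariate, and the plan states no estimate or interval to go with it.

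The smaller group has 40 people, so a non-significant result is quite possible even if iteration helped. The article's caveats do not cover this comparison. The remark in the Analysis Plan about initial effect sizes concerns asthma control over four weeks. The Discussion's warning about significance concerns asthma control over 28 days and sex or age differences. Nothing tells the reader how to take a null result for alpha against beta. The Discussion also says that the results will feed the design of later health chatbots, and for that purpose the size and uncertainty of any gain are more useful than a test result.

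**Working it through.** The article gives no power, significance level, effect size or SD for this comparison, so there is no stated figure to reproduce. The group sizes are consistent: 20 + 20 + 260 = 300.

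**Inputs from the article:** alpha n = 40, beta n = 260.

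**Assumed:** two-sided 5% level; normally distributed outcome with a common SD; relative efficiency of the rank test 3/π = 0.955; true shifts of 0.2 to 0.5 SD; pre-post ACQ correlation ρ of 0.5 to 0.7; full data first, then 30% loss.

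**Rank test.** The standard error of the difference, in SD units, is √(1/40 + 1/260) = 0.170. Allowing for rank efficiency, it is 0.170/√0.955 = 0.174. Power is Φ(d/0.174 − 1.96).

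| True shift d (SD) | Power, 40 v 260 | Simulated Kruskal-Wallis (10,000 runs) | Power, 30% loss (28 v 182) |
|---|---|---|---|
| 0.2 | 21% | 21% | 16% |
| 0.3 | 41% | 40% | 30% |
| 0.4 | 63% | 62% | 49% |
| 0.5 | 82% | 82% | 67% |

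The shift detectable with 80% power is 2.80 × 0.174 = 0.49 SD with full data and 0.58 SD with 30% loss. If the test were run on three batches (20/20/260), with the second assumed to lie halfway, simulated power at 0.3 SD would be 21%.

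**Adjusting ACQ for baseline (linear model).** The residual SD is √(1 − ρ²): √0.75 = 0.866 for ρ = 0.5, and √0.51 = 0.714 for ρ = 0.7. Power at 0.3 SD is then:

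- ρ = 0.5: Φ(0.3/(0.170 × 0.866) − 1.96) = 53%
- ρ = 0.7: Φ(0.3/(0.170 × 0.714) − 1.96) = 70%

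The unadjusted linear figure is 42%, so nearly all of the gain comes from the baseline and not from leaving the rank test.

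**Precision.** The unadjusted 95% CI half-width is 1.96 × 0.170 = 0.33 SD. With adjustment it is 0.33 × 0.866 = 0.29 SD or 0.33 × 0.714 = 0.24 SD.

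**Change scores, for comparison.** With equal SDs before and after, the variance of the change is 2(1 − ρ) times the outcome variance: 1.00 for ρ = 0.5 and 0.60 for ρ = 0.7. The corresponding figures with adjustment are 0.75 and 0.51. Ranking change scores would use the baseline, but less efficiently.

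**The case against.** The strongest reply is that this is a condensed article about a feasibility study. It names a test, and reporting details normally sit in a fuller plan. Several stronger readings are tempting, and the document does not support them:

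- **That only a P value will be reported.** The article does not say so and excludes no medians, estimates or intervals. The point is that none is specified for this question.
- **That the result would have no direction or size.** With two groups, direction can be read from the mean ranks or medians. The probability of superiority comes from the same ranks: it is the Wilcoxon U divided by the product of the group sizes. The test need not be discarded for this reason.
- **That the test cannot use baseline ACQ.** It could be run on change scores, and the plan's reference to effects may mean that. No such use is stated, and the calculation above shows that it would be less efficient.
- **That a real improvement would usually be missed.** This holds with full data for shifts up to about 0.3 SD, but not at 0.4 SD (63%) or 0.5 SD (82%). The article states no expected effect, so no general claim is possible.

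Two further objections stand. Baseline adjustment helps only the ACQ. It also cannot make alpha and beta a fair comparison. Alpha uses the chatbot for 1 week and beta for 28 days, at a later date and from largely different sources. The three channels other than YouGov supply 3 × 60 = 180 people, so a beta group of 260 would also need 80 from YouGov, and the channels may overlap in part. A better estimate of this contrast is still not an estimate of the effect of iteration.

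The mismatch itself remains: a question about improvement is paired with an unadjusted test of difference, and the article's caveats do not reach it.

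**Conclusion.** The point holds in a limited form. For the iteration question the plan fixes an unadjusted Kruskal-Wallis test of 40 against 260 and specifies no effect measure, interval or use of baseline ACQ. Power is about 21%, 41%, 63% and 82% for shifts of 0.2, 0.3, 0.4 and 0.5 SD, so non-significance would not be evidence of no effect. Using baseline ACQ would raise power at 0.3 SD from about 41% to about 53–70% for that outcome, and would lessen bias from baseline differences in asthma control between groups that were not randomised.

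The power figures rest on an assumed two-sided 5% level, normal shifts and complete data. The gain from adjustment also rests on an assumed correlation of 0.5–0.7 and a linear model, and it was not computed for ordinal regression. Confounding by length of use, channel and calendar time is a larger, separate problem that remains whatever analysis is chosen.

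**What to change.** Amend the Analysis Plan as follows.

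1. For ACQ, compare the phases with a model that includes baseline ACQ as a covariate (ANCOVA or ordinal regression), and report the adjusted difference or odds ratio with its 95% CI.
2. For outcomes without a baseline, keep the rank test if preferred, and report the probability of superiority or the median difference with its 95% CI beside it.
3. State that a non-significant difference is not evidence that iteration had no effect.
4. State that the estimate is descriptive, because alpha and beta also differ in length of use, recruitment channel and calendar time, and that the adjustment does not remove these differences.

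The cost is slightly more analysis work and a model assumption for ACQ. No extra data are needed, since ACQ is already planned at both times.
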